## Abstract

**Background:**

The hospital experience is often marked by fear and pain, particularly for children undergoing medical procedures. Sedation is commonly used to alleviate patient anxiety, but it poses additional health risks. Caregivers, usually the parents, also experience emotional distress during the child’s hospital stay, which can further exacerbate the child’s anxiety and pain. While various interventions exist to ease patient distress, few consider the emotional well-being of caregivers.

**Objective:**

This study aims to explore the effectiveness of a cooperative virtual reality (VR) game as a novel nonpharmacological solution to reduce anxiety and pain for both pediatric patients and their caregivers during medical procedures. Specifically, we aim to investigate whether the VR game “Sweet Dive VR” (SDVR), designed for children aged between 6 and 12 years to play with 1 caregiver, can alleviate anxiety and pain during different types of needle punctures and Kirschner-wire removal.

**Methods:**

A prospective multicenter randomized clinical trial will be conducted. Eligible participants will be identified by scanning the hospital information system, and group allocation will follow stratified randomization. During the medical procedure, patients in the VR condition will play SDVR with a caregiver present, while patients in the control group will listen to a recording of gently crashing waves. Data collection will be carried out through self-reports of patients and caregivers using visual analog scales and questionnaires at 2 measurement time points: before and after the intervention. In addition, observation by the interviewers will occur during the intervention to capture emotional and pain reactions as well as interaction quality between patients and caregivers and smoothness of the procedure flow using a structured observation protocol. The measured variables will encompass patient affect and pain, caregiver affect, player experience, patient experience, and the flow of the procedure.

**Results:**

As of November 2024, we enrolled 39 patients and caregivers, 28 of whom completed the study. Data collection is still ongoing.

**Conclusions:**

Cooperative VR gaming, as exemplified by SDVR, emerges as a promising intervention to address anxiety and pain in pediatric patients while involving caregivers to support the emotional well-being of both parties. Our approach strives to foster positive shared experiences and to maintain trust between children and caregivers during emotionally challenging medical situations.

**Trial Registration:**

German Clinical Trial Register (DRKS) DRKS00033544; https://drks.de/search/en/trial/DRKS00033544

**International Registered Report Identifier (IRRID):**

DERR1-10.2196/63098

## Introduction

### Background

Fear and pain characterize the hospital experience. Children, due to a lack of understanding of the situation, often show extreme anxiety reactions even in objectively harmless situations such as magnetic resonance imaging [1]. Hence, the patient’s anxiety and stress can complicate treatment procedures and interfere with the healing process [2-4]. As a result, it is a common practice to sedate patients by administering medication. However, the use of such medication is associated with additional health risks [5], particularly in the context of child development [6]. An additional factor that can influence the emotional experience of child patients is their caregivers, in most cases a parent. Caregivers are also under extraordinary emotional pressure during the child’s stay in hospital. If a medical procedure causes intense fear or pain, it can strain the caregiver-child relationship, especially if the child perceives the caregivers as siding with medical staff instead of supporting them—for example, by helping to physically restrain the child [7]. As a result, anxiety, stress, and pain of patient and caregiver can mutually depend on and reinforce each other [8]. While there are numerous pharmacological and nonpharmacological options to ease the patient, the experience of the caregivers is rarely the focus of such interventions.

Therefore, it is advisable to explore nonpharmacological solutions to reduce anxiety and pain. Distracting patients from the medical situation in a controlled manner is an approach that has proven successful for a large variety of media such as movies, music, or toys [9]. The use of immersive technologies such as digital games and virtual reality (VR), in particular, has been shown to be effective in reducing anxiety and pain in a variety of medical situations in numerous studies, especially for needle-related procedures, burn care, and in dental medicine [9-13]. However, these solutions typically address only the patient, which may lead to patients and caregivers feeling disconnected from each other. VR has the potential to result in patients feeling separated from their caregivers due to the sensory shielding provided by wearing a head-mounted display (HMD), which is necessary to create the desired level of immersion. This, in turn, could have an unintended anxiety-increasing effect.

### Approach

We are pursuing a new approach in our work: we have developed the cooperative, asymmetrical VR game “Sweet Dive VR” (SDVR) that involves the patient and a caregiver equally in the gameplay and promotes joint communication [14]. In this way, both parties are distracted from the intimidating medical situation without being artificially separated from each other. Involving caregivers in the game, thereby creating positive shared player experiences, can be a way of maintaining children’s trust and reducing feelings of helplessness for both children and caregivers [15]. In addition to the game-related interaction with the child, the caregivers are given the task of reacting to certain steps of the medical procedure (eg, the application of a disinfectant or an oxygen cannula) by triggering in-game events. In this way, we achieve synchronization of the virtual world with the patient’s real-world sensory impressions, which is intended to preserve and strengthen immersion for the patient on the one hand, while supporting the caregivers’ sense of agency. SDVR was designed for children aged between 6 and 12 years and for application during needle-related procedures, in particular port punctures, bone marrow punctures, central and peripheral venous catheterization, and venipunctures. However, we are also planning to test our approach with more painful procedures, such as Kirschner-wire removal.

### Objectives

While several different works have successfully used VR games as a distraction during painful procedures [14-16], SDVR is, to the best of our knowledge, the first game that involves both the patient and the caregiver and aims to enhance the emotional experience of both. This study aims to evaluate the effectiveness of using cooperative VR games during medical procedures to improve patient and caregiver experiences. Specifically, we examine whether SDVR can reduce patients’ anxiety, pain, and agitation; improve cooperation; and positively influence caregivers’ emotional states compared to a control condition in which a calming atmosphere is created by playing natural ocean wave sounds to promote relaxation.

## Methods

### Hypotheses

In this study, we investigate whether targeted distraction from anxiety- and pain-inducing medical procedures through cooperative VR gaming can reduce experienced pain and anxiety while fostering well-being for both the patients and their caregivers. A list of our hypotheses is presented in Textbox 1. Hence, the primary outcome of the study is a reduction in pain and anxiety ratings of the patient (hypothesis 1) as well as an improvement in the caregiver’s emotional experience (hypothesis 2). Our intervention relies on targeted distraction through sensory immersion for the patient as well as cognitive immersion and game fun for the patient and caregiver. Thus, distraction from the medical procedure represents a further end point of the study (hypothesis 3 and hypothesis 5).

The smooth execution of the medical procedure, characterized by the cooperativeness of the patient and caregiver, the needlessness of sedation or fixation, and an uninterrupted flow, will be assessed as a secondary end point (hypothesis 4). Moreover, this study aims to evaluate the quality of SDVR with respect to the player experience of both patient and caregiver (hypothesis 5).

A list of hypotheses.
**Hypothesis 1: patient affect and pain**
Patients playing Sweet Dive VR (SDVR) during the procedure will report reduced levels of *anxiety* compared with those in the control group.Patients playing SDVR during the procedure will report reduced levels of *pain* compared with those in the control group.Patients playing SDVR during the procedure will exhibit decreased *motoric activity* compared with those in the control group.*Observer’s* ratings of *patient cooperation* during the procedure will be improved in the SDVR group compared with those in the control group.*Caregivers’* ratings of patient *pain* will be lower in the SDVR condition than in the control condition.*Caregivers’* ratings of patient *anxiety* will be lower in the SDVR condition than in the control condition.*Observers’* ratings of patient *pain* will be lower in the SDVR condition than in the control condition.*Observers’* ratings of patient *anxiety* will be lower in the SDVR condition than in the control condition.
**Hypothesis 2: caregiver affect**
Caregivers in the SDVR group will experience more *positive emotions* during the procedure compared with those in the control group.Caregivers in the SDVR group will experience fewer *negative emotions* during the procedure compared with those in the control group.*Observer’s* ratings of *caregiver cooperation* during the procedure will be improved in the SDVR group compared with those in the control group.
**Hypothesis 3: player experience**
The more positive the player experience of the patients in the SDVR group is, the lower will be the *patients'* intensity of *anxiety* during the procedure.The more positive the player experience of the patients in the SDVR group is, the lower will be the *patients'* intensity of *pain* during the procedure.The more positive the playing experience of the *caregivers* in the SDVR group, the less negative will their *emotional experience* be.

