**Hypothesis 4: patient experience**
In the SDVR condition, more patients will have a feeling of *being in control over the situation* than those in the control condition.In the SDVR condition, more patients will report being *distracted* from the procedure than those in the control condition.The number of *patients* reporting that SDVR reduced their *agitation* will be greater than those reporting that listening to ocean waves reduced their agitation.*Patients* in the SDVR condition will be more *surprised by the pain* than those in the control condition.

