### Potential Confounding and Influencing Factors

The meta-analysis carried out by Eijlers et al [11] indicates that VR-based distraction from anxiety and pain is more efficacious in younger children than in older children. Age and gender influence the perception of pain and anxiety during medical procedures. Younger children tend to report more pain during procedures such as venipuncture [16]. In self-reporting, girls tend to report more pain than boys [17]. However, older children and boys tend to rate pain and anxiety differently compared to younger children and girls [17]. Age and parental predictions of distress are substantial predictors of pain and anxiety on blood tests [18]. Therefore, age and gender will be considered as possible influencing factors in the analysis.

Our intervention addresses a range of medical procedures that have shown to be highly anxiety- and stress-inducing in pediatric patients but can generally be performed without anesthesia. It is possible that patient anxiety and pain ratings differ for different procedures and that these perceptions influence the effect of our intervention.

Fundamental anxiety as a patient characteristic (ie, trait anxiety) is also a likely influencing factor for anxiety and pain ratings [19]. Furthermore, there is evidence in the literature of a link between perceived anxiety and postoperative recall of pain [20], which could influence patients’ retrospective assessment of their pain. Therefore, we will consider the assessment of the caregivers and the observation of the interviewers in our study.

A well-documented phenomenon that negatively impacts the VR gaming experience is simulator sickness, which includes symptoms such as nausea, dizziness, headaches, and eye strain. There is evidence that children are less likely to react to VR exposure with these negative symptoms [21], but there have been few studies on the possible relationship between age and different forms of visually induced motion sickness. Nevertheless, we will record any indications of simulator sickness before and after the intervention as the described symptoms may relate to patients’ general health state. We have elaborated more on that topic in the Methods section, under the Simulator Sickness subsection.

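### The distraction end point is assigned to a non-randomised association inside the SDVR arm, while the randomised comparison of reported distraction stands under a different hypothesis number

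*Protocol article*

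**What the plan says.** The Hypotheses section of the protocol article describes an intervention that works through immersion and enjoyment of the game, and concludes: "Thus, distraction from the medical procedure represents a further end point of the study (hypothesis 3 and hypothesis 5").

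In the list of hypotheses:

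- **Hypothesis 3 (player experience)** concerns the SDVR arm only. For children: "The more positive the player experience of the patients in the SDVR group is, the lower will be the" intensity of anxiety and, separately, of pain. For caregivers, a better playing experience "in the SDVR group, the less negative will their" emotional experience be.
- **Hypothesis 4 (patient experience)** includes a comparison of how many children report being distracted under SDVR and under control.
- **Hypothesis 5 (flow of the procedure)** is the observers' rating of overall procedure quality.

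The same Hypotheses section, however, uses number 4 for the smooth running of the procedure and number 5 for player experience. Neither agrees with the list.

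Under Potential Confounding and Influencing Factors the article states: "Fundamental anxiety as a patient characteristic (ie, trait anxiety) is also a likely influencing factor for anxiety and pain ratings". For the analysis it says that "age and gender will be considered as possible influencing factors in the analysis". Table 1 places the children's adapted PXI at the post-intervention measurement, together with STAIC-S, VAS anxiety and VAS pain. It places the caregivers' PXI at the same measurement as their post-intervention PANAS. Baseline scores are collected: STAIC-T at screening, and STAIC-S, VAS anxiety and the caregivers' PANAS before the intervention.

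**The concern.** The null tested by hypothesis 3 is that player experience and anxiety (or pain, or caregiver affect) are uncorrelated within the SDVR arm. The null that matters for a distraction claim is that playing does not distract, or does not lower anxiety or pain. The first can be false while the second is true.

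There are two routes to that. One is a common cause: an anxious child may both enjoy the game less and report more anxiety afterwards. The article supplies the first link by naming trait anxiety as a likely influence on the ratings. Its Challenges section makes the second link plausible, noting that children with bad earlier experiences may find the headset a burden. The other route is reverse direction: a child who was hurt or frightened marks the game down. Minimisation on trait anxiety balances the two arms, but does nothing for a correlation within one of them.

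At stake is the mechanism conclusion. A positive hypothesis 3, tied to the distraction end point, invites the reading that immersion and fun lowered anxiety and pain.

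**Working it through.** **The plan's own figure.** Two-sided t test, alpha 0.05, power 80%, 39 per group: the noncentral t gives a detectable d of 0.643, which agrees with the stated 0.64. That calculation covers a two-group comparison, not the hypothesis 3 correlations, but it fixes n = 39 in the SDVR arm.

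**Threshold for hypothesis 3.** With n − 2 = 37 degrees of freedom, t = 2.026, so the critical |r| = 2.026/√(37 + 2.026²) = 0.316.

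**Common-cause model.** Baseline anxiety correlates a with post-procedure anxiety and −b with player experience. Play has no effect on anxiety. The induced correlation is then r = −ab. The chance of a significant result in the predicted direction is about Φ(√(n−3)·atanh(ab) − 1.96), with √36 = 6. The documents give no values for a or b, so these are assumptions shown over a range. Simulations used 20,000 runs per setting. The adjusted columns are partial correlations given baseline anxiety, measured either without error or with reliability 0.8.

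| a, b | r | Formula, n = 39 | Simulated, n = 39 | Adjusted, no error | Adjusted, reliability 0.8 |
|---|---|---|---|---|---|
| 0.3, 0.3 | −0.09 | Φ(6×0.0902 − 1.96) = 8% | 7.6% | 2.4% | 3.0% |
| 0.5, 0.3 | −0.15 | Φ(6×0.1511 − 1.96) = 15% | 14.5% | 2.5% | 4.2% |
| 0.5, 0.5 | −0.25 | Φ(6×0.2554 − 1.96) = 33% | 34.0% | 2.5% | 5.8% |
| 0.6, 0.5 | −0.30 | Φ(6×0.3095 − 1.96) = 46% | 46.7% | 2.5% | 6.9% |
| 0.7, 0.6 | −0.42 | Φ(6×0.4477 − 1.96) = 77% | 77.9% | 2.6% | 11.3% |
| 0.7, 0.7 | −0.49 | Φ(6×0.5361 − 1.96) = 90% | 90.0% | 2.3% | 15.9% |

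The nominal rate in one direction is 2.5%. In the same simulations the randomised between-arm t test stayed at about 5% two-sided.

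**Fewer completers.** The Results section reports 28 of 39 enrolled as completed (72%, both arms together). If 72% of 39, that is 28, completed in the SDVR arm, the unadjusted rates are 6.7% at 0.3/0.3, 25% at 0.5/0.5 and 78% at 0.7/0.7.

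**Reverse direction.** Let baseline anxiety correlate 0.5 with post-procedure anxiety, and let post-procedure anxiety itself lower the game rating with slope −0.3 or −0.5. At n = 39 the unadjusted test is significant in 46% and 92% of trials, and the test adjusted for baseline anxiety still in 36% and 82%.

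**Numbering.** By the list, the distraction end point rests on the within-arm association (3) and the procedure rating (5), and the latter does not measure distraction. By the Hypotheses section's own descriptions, 5 is player experience and 4 is procedure flow, which would leave 3 for patient experience. On both readings the player-experience hypothesis is assigned to distraction.

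The simulation covers the anxiety part. The pain and caregiver parts have the same structure.

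**The case against.** The strongest reply has four parts.

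- **No model is fixed.** The article says only that descriptive and inferential statistics will be used, and an analysis plan that is not shown could adjust for baseline anxiety. This stands. A reader might infer that the test will be unadjusted, or that age and gender are the only covariates, but the article says neither. The defect that remains is in what the article does state: which hypothesis carries the end point. Adjustment alone would not repair that.
- **The numbering may simply be off.** If the Hypotheses section follows an order in which 3 is patient experience, the randomised comparison is cited after all. This is possible, and a reader should not infer that hypothesis 3 is the only test of distraction. Player experience would still be cited beside it, as hypothesis 5, and the two numberings still need to be reconciled.
- **The wording is associational and the efficacy claim lies elsewhere.** Hypotheses 1 and 2 are primary and compare randomised arms. This is correct, and it limits the point to the mechanism conclusion.
- **Interviewers also rate the child's play.** The Player Experience section provides for this, and hypothesis 3 does not say whose rating is used. An interviewer rating would remove the shared rater for children. It would not remove the common cause, and the interviewer watches the child's distress during the same procedure.

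**Conclusion.** The point holds for the assignment of the end point and for the interpretation of the player-experience hypothesis. A within-arm association of a non-randomised rating cannot carry a distraction end point. With an inert game it would be significant in the predicted direction in about 8% to 90% of trials for a and b between 0.3 and 0.7 at n = 39, against 2.5%. The width of that range reflects assumed correlations, not figures in the article.

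It would be too strong to say that the test turns significant whenever calmer children enjoy the game more. At assumed correlations of 0.3 it does so in only about 8% of trials, and the chance passes one half only when the confounded correlation is somewhat stronger than −0.30. Nor does the point reach the trial's main conclusions: the between-arm tests of anxiety, pain and caregiver affect in hypotheses 1 and 2 are unaffected.

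**What to change.** 1. In the Hypotheses section, correct the cross-references to match the list, and let the distraction end point rest on the between-arm comparison of reported distraction in hypothesis 4.
2. Describe the player-experience hypothesis as an exploratory association within the SDVR arm, not as evidence that distraction occurred or lowered anxiety or pain.
3. Analyse it by regression or partial correlation with a small set of baseline scores: STAIC-T and pre-procedure STAIC-S or VAS anxiety for children, and pre-procedure PANAS for caregivers.
4. State that adjustment reduces confounding without removing it (about 3% to 16% false positives at baseline reliability 0.8 in the settings above) and does not address reverse direction.

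The cost is a wording change, two degrees of freedom for the children's models and about one for the caregivers', and a more modest mechanism claim. The covariate set should stay small. The Sample section lists five procedure types, so adding procedure type would take four more degrees of freedom from at most 39 children. All the scores are already collected, and no extra patients or visits are needed.

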**Hypothesis 4: patient experience**
In the SDVR condition, more patients will have a feeling of *being in control over the situation* than those in the control condition.In the SDVR condition, more patients will report being *distracted* from the procedure than those in the control condition.The number of *patients* reporting that SDVR reduced their *agitation* will be greater than those reporting that listening to ocean waves reduced their agitation.*Patients* in the SDVR condition will be more *surprised by the pain* than those in the control condition.
**Hypothesis 5: flow of the procedure**
The *observers’* rating of the *overall quality of the procedure* will be higher in the SDVR condition than in the control condition.

As interviewing children about their emotional and physical experience is a methodological challenge due to various biases, and because we strive for an objective assessment of the patient’s and caregiver’s experience, we follow a comprehensive, holistic approach in our methodology and the instruments used. In addition to the patients’ and caregivers’ self-reported emotional experiences, we also ask the caregivers to assess the patient’s anxiety and pain. In addition, the interviewers use a structured observation protocol to assess the patient’s experience, the gaming situation, and the course of the medical procedure.

